# A multi-centre open-label randomised non-inferiority trial comparing watchful waiting to antibiotic treatment for acute otitis media without perforation in low-risk urban Aboriginal and Torres Strait Islander children (the WATCH trial): study protocol for a randomised controlled trial

**DOI:** 10.1186/s13063-016-1247-y

**Published:** 2016-03-03

**Keywords:** Otitis media, Acute otitis media, Aboriginal and Torres Strait Islander peoples, Indigenous population, Children, Antimicrobial agents, Randomised controlled trial

## Abstract

**Background:**

Treatment guidelines recommend watchful waiting for children older than 2 years with acute otitis media (AOM) without perforation, unless they are at high risk of complications. The high prevalence of chronic suppurative otitis media (CSOM) in remote Aboriginal and Torres Strait Islander communities leads these children to be classified as high risk. Urban Aboriginal and Torres Strait Islander children are at lower risk of complications, but evidence to support the subsequent recommendation for watchful waiting in this population is lacking.

**Methods/Design:**

This non-inferiority multi-centre randomised controlled trial will determine whether watchful waiting is non-inferior to immediate antibiotics for urban Aboriginal and Torres Strait Islander children with AOM without perforation. Children aged 2 − 16 years with AOM who are considered at low risk for complications will be recruited from six participating urban primary health care services across Australia. We will obtain informed consent from each participant or their guardian. The primary outcome is clinical resolution on day 7 (no pain, no fever of at least 38 °C, no bulging eardrum and no complications of AOM such as perforation or mastoiditis) as assessed by general practitioners or nurse practitioners. Participants and outcome assessors will not be blinded to treatment. With a sample size of 198 children in each arm, we have 80 % power to detect a non-inferiority margin of up to 10 % at a significance level of 5 %, assuming clinical improvement of at least 80 % in both groups. Allowing for a 20 % dropout rate, we aim to recruit 495 children.

We will analyse both by intention-to-treat and per protocol. We will assess the cost- effectiveness of watchful waiting compared to immediate antibiotic prescription. We will also report on the implementation of the trial from the perspectives of parents/carers, health professionals and researchers.

**Discussion:**

The trial will provide evidence for the safety and effectiveness of watchful waiting for the management of AOM in Aboriginal and Torres Strait Islander children living in urban settings who are considered to be at low risk of complications.

**Trial registration:**

The trial is registered with Australia New Zealand Clinical Trials Registry (ACTRN12613001068752). Date of registration: 24 September 2013.

## Background

Acute otitis media (AOM) is a common reason for childhood presentation to health services and for prescription of antibiotics [1] and is commonly managed in general practice in Australia [2]. AOM creates a large health and cost burden for individuals and communities [1, 3]. Otitis media (OM) refers to inflammation of the middle ear space, which is characterised by the presence of middle ear effusion and causes illness and hearing loss [1]. In AOM there are also symptoms and signs of acute infection [4]. Serious complications of AOM, such as chronic suppurative otitis media (CSOM) (persistent ear discharge through a perforation in the eardrum) and mastoiditis, are rare in developed countries, where most cases of AOM resolve spontaneously [1, 5].

Antibiotics are not recommended for most children in developed countries with AOM due to limited clinical benefit [4] and the personal and public health risks of antibiotic resistance [6–8]. Aboriginal and Torres Strait Islander children who live in remote communities, where the incidence of AOM and prevalence of CSOM are high, are among those who are to expected benefit from antibiotic treatment for AOM [9–11]. However, there is little evidence for the appropriate management of AOM in the majority of Aboriginal and Torres Strait Islander children who live in urban settings and who are considered to be at lower risk of complications.

### Diagnosis and management of AOM

The particular combination of symptoms and signs of acute infection providing the most reliable diagnosis of AOM is debated. However, middle ear effusion accompanied by ear pain or bulging of the tympanic membrane is likely to be AOM [4].

High-level evidence from studies in developed countries shows that immediate antibiotic treatment confers only a modestly decreased duration of pain and fever at the cost of increased side effects [12–17]. International treatment guidelines [18, 19] currently recommend watchful waiting (initial observation and symptomatic treatment) and avoidance of immediate antibiotic treatment of AOM in children older than 2 years of age who are at low risk of complications. In this approach, carers are advised that children with persistent symptoms need clinical reassessment, at which point the clinician will review the need for antibiotics.

### OM and AOM management in urban Aboriginal and Torres Strait Islander children

Data on the burden of OM in Aboriginal and Torres Strait Islander children living in urban areas are sparse. Moderate to severe hearing loss was present in 32 % of 47 Aboriginal children and 7 % of 120 non-Aboriginal children aged 12 months or more in a study undertaken in an urban area of Western Australia [20]. In the most recent Australian Aboriginal and Torres Strait Islander Health Survey, 12 % of children under 14 years were reported to have ear or hearing problems, and this was the same in remote and non-remote areas [21]. Aboriginal and Torres Strait Islander children were significantly more likely than non-Indigenous children to be reported to have ear or hearing problems (rate ratio 1.3) [21]. As many Aboriginal and Torres Strait Islander Australians already experience marked disadvantage compared to other Australians, effective treatment of ear disease and prevention of hearing impairment in Aboriginal and Torres Strait Islander children is vital to maximise health and learning outcomes [22].

Recently, the recommended approach to the management of Aboriginal and Torres Strait Islander children with AOM has changed. The 2001 Australian guidelines [23] recommended immediate antibiotics for all Aboriginal and Torres Strait Islander children with AOM. However, the 2010 guidelines [5] recommend watchful waiting for Aboriginal and Torres Strait Islander children at low risk of CSOM. In these guidelines, Aboriginal and Torres Strait Islander children are classified as low risk if they are older than 2 years of age, do not have eardrum perforation or history of perforation and do not live in geographical areas with a high incidence of CSOM (defined as greater than 4 %), such as is consistently seen in remote Australia. As approximately 75 % of Aboriginal and Torres Strait Islander children live in urban and non-remote regional communities [24], where CSOM rates are likely to be less than 2 % [25, 26], this advice presents an important change in clinical practice [5].

### Pilot work undertaken prior to commencement of the study

An obstacle to evidence-based management of OM in primary care is lack of diagnostic accuracy [1, 27]. Diagnosis of AOM requires detection of middle ear effusion, which can only be reliably made using tympanometry or pneumatic otoscopy. However, both of these diagnostic aids are greatly underutilised by general practitioners (GPs), including in Aboriginal Medical Services [28]. Prior to the development of the WATCH study design, we undertook preliminary research concerning diagnosis of OM in the general practice setting [29, 30]. We determined that tympanometry was likely to be a more acceptable diagnostic technique than pneumatic otoscopy to aid GP diagnosis in AOM and incorporated this into the study design. We also undertook a retrospective medical record review in two participating services prior to commencement of the study to determine the numbers of children seen with AOM at these sites. This information was used to determine the study design and the duration required to meet recruitment targets.

### Study aims

The WATCH trial aims to determine whether watchful waiting is non-inferior to immediate antibiotic treatment in achieving clinical resolution of AOM without complications in Aboriginal and Torres Strait Islander children at low risk of complications who reside in urban areas. In addition to providing information to guide clinical management of AOM, we will investigate the relative costs and acceptability of the two treatment approaches to parents/carers and health care providers, and their views and experiences of the research processes.

## Methods/Design

### Primary objective

To determine whether watchful waiting is non-inferior to immediate antibiotic treatment in achieving clinical resolution of AOM without perforation at day 7 in urban Aboriginal and/or Torres Strait Islander children who are at low risk of CSOM.

### Secondary objectives

To determine whether watchful waiting is non-inferior to immediate antibiotic treatment in regards to symptom resolution, resolution of otoscopic signs, complication rates, and parent/carer satisfaction with treatmentTo assess the cost-effectiveness of watchful waiting compared to immediate antibiotic prescriptionTo explore the acceptability of the two treatment arms and the experience of taking part in and conducting the trial, from the perspectives of parents/carers, health professionals and researchers, and to use this information to assist in the interpretation and translation of the findings

### Design

We are using a non-inferiority, open-label, randomised controlled trial (RCT) design. Non-inferiority studies seek to determine if a new treatment is no worse than a reference treatment by a predetermined margin. The new treatment is recommended if it is similar or better than the previous treatment, usually on the premise that the new treatment has other advantages over the reference treatment [31]. Children will be randomised to watchful waiting or immediate antibiotic therapy, stratified by study site and age of child (2 − 6 years and 7 − 16 years), using the National Health and Medical Research (NHMRC) Clinical Trial Centre Interactive Voice Response System (IVRS). It is not possible to blind the patient or treating staff. Outcome measurements will be verified by blinded assessment of tympanometry and video-pneumatic otoscopy (VO) data by an otolaryngologist and analysis will be blinded.

For practical reasons, the participating sites will commence staggered recruitment, commencing in two sites per block, 6 months apart. We will undertake cost-effectiveness analysis and a qualitative study in conjunction with the RCT as an integral part of the study design, with planning for both having commenced at inception [32]. A Data Safety Monitoring Board will oversee the conduct of the trial.

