### Primary outcome

Proportion of children with clinical resolution of AOM, defined as all of the following: no pain, fever not higher than 38 °C, no bulging eardrum and no complications of OM (no perforation or mastoiditis) assessed by:GP or nurse practitioner clinical examination on day 7 (acceptable range days 5 − 10)Where 1. is not available, GP or nurse practitioner assessment of parental report and review of VO (recorded by trained RO), and no fever of at least 38 °C

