### Secondary outcomes

Proportion of children with resolution of signs of AOM, through blinded otolaryngologist assessment of VO images and tympanometry taken at days 0 and 7* by a trained ROProportion of children with middle ear effusion, perforation and CSOM at week 7*, assessed by an independent blinded observer (otolaryngologist) reviewing VO and tympanometry dataProportion of children with new antibiotic prescriptions (where ‘new’ is any antibiotic prescription provided after the recruitment consultation) for an index case of AOM assessed by review of medical record and by parent/carer reportParent/carer-reported time to resolution of AOM symptoms assessed by parent/carer symptom report at days 3*, 7* and 14*, including the AOM Faces Scale [37]Usage of analgesia for AOM symptom relief assessed by parent/carer reportParent/carer satisfaction with AOM treatment assessed by parent/carer report using rating scale

(*acceptable ranges: days 2 − 4; days 5 − 10; days 11 − 17; weeks 6 − 8)

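### The blinded otolaryngologist read is presented as verifying outcomes, but no stated primary or sensitivity analysis uses it; it reaches the results only through secondary outcomes

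*Protocol article*

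**What the plan says.** All references are to the protocol article.

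- **Design** concedes that "It is not possible to blind the patient or treating staff" and then offers a safeguard: "Outcome measurements will be verified by blinded assessment of tympanometry and video-pneumatic otoscopy (VO) data by an otolaryngologist". It does not say which outcomes are meant or what follows if the reader disagrees. It adds that the analysis will be blinded, which concerns the analyst and not the scoring of the child.
- **Abstract, Methods/Design**: "Participants and outcome assessors will not be blinded to treatment".
- **Primary outcome** is a composite of pain, fever, bulging and complications. The first route is "GP or nurse practitioner clinical examination on day 7". If there was no examination, the GP or nurse practitioner scores the child from the parent's report, the video-otoscopy (VO) recording and temperature. The otolaryngologist has no part in either route.
- **Secondary outcomes** is where the blinded day-7 read appears, as "resolution of signs of AOM, through blinded otolaryngologist assessment of VO images and tympanometry". A further blinded read at week 7 covers effusion, perforation and CSOM.
- **Secondary objectives** include non-inferiority for otoscopic signs.
- **Analysis** takes the primary outcome as already defined, by intention to treat and per protocol, and lists five sensitivity analyses.

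**The concern.** In an open-label non-inferiority trial, a blinded check on the endpoint is a main protection against assessors' knowledge of the arm. The Design section tells the reader that this protection exists. The endpoint, the decision rule and the sensitivity list, as fixed elsewhere, do not provide it for the primary outcome.

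Two of the composite's elements, bulging and perforation, can be seen on VO and could be checked blind. If the unblinded assessor reads the watchful-waiting ears leniently, the difference shrinks and a false non-inferiority claim becomes more likely. If the assessor reads them harshly, power is lost. Neither would show in the primary result or in any listed sensitivity analysis.

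**Working it through.** **1. Does the blinded read reach the primary result?**

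| Place in the article | Who judges | Uses the blinded read? |
|---|---|---|
| Primary outcome, examination route | GP/nurse practitioner | No |
| Primary outcome, fallback route | GP/nurse practitioner reviewing VO | No |
| Sensitivity 1 and 2: missing as failure, missing as success | As above | No |
| Sensitivity 3: extrapolation from the days 2–4 interview | Interview data | No |
| Sensitivity 4 and 5: best and worst case for watchful waiting | As above | No |
| Secondary outcomes, day 7 and week 7 | Otolaryngologist | Yes |

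The intention-to-treat and per-protocol analyses differ in who is included, not in who judged the ear.

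**2. Could the day-7 secondary outcome stand in for verification?** Only in part. It combines VO with tympanometry and leaves out pain and fever. If it differed from the primary result, one could not tell whether assessor bias or the different construct was the cause.

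**3. The plan's own sample size, reproduced.** Inputs from Sample size and power: 80% in both arms, margin 10 points, 80% power, significance level 5% (sidedness not stated).

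- n per arm = (z_α + z_β)² × [p₁(1−p₁) + p₂(1−p₂)] / margin²
- One-sided 5%: (1.645 + 0.842)² × 0.32 / 0.01 = 198, as stated. Then 396 / 0.80 = 495, as stated.
- One-sided 2.5% (a two-sided 95% CI) would give 252 per arm. That is a separate matter, but it is why both conventions appear below.

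**4. Illustrative size.** The documents give no misclassification rates, so f is an assumption: the net fraction of watchful-waiting failures called resolved, with the antibiotic arm read correctly. True rates are 80% (antibiotic) and 70% (watchful waiting), exactly at the margin.

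- Observed watchful-waiting rate p_W = 0.70 + 0.30f
- SE = √[(0.80×0.20 + p_W(1−p_W)) / 198]
- P(claim non-inferiority) = Φ[(p_W − 0.80 + 0.10)/SE − z]

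| f | p_W | SE | (p_W − 0.70)/SE | z = 1.96 | z = 1.645 |
|---|---|---|---|---|---|
| 0 | 0.700 | – | 0 | 2.5% | 5.0% |
| 5% | 0.715 | 0.0429 | 0.350 | 5.4% | 9.8% |
| 10% | 0.730 | 0.0425 | 0.706 | 10.5% | 17.4% |

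**5. What range of f is plausible?** Correcting a misread ear sign changes the result only for children who fail on that sign alone. If 25–50% of failures were of that kind (assumption) and 20% of those were misread (assumption), f = 0.25 × 0.20 to 0.50 × 0.20 = 5% to 10%.

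**6. The opposite direction.** With true rates of 80% in both arms and watchful waiting scored 2 points too low, power under the two-sided 95% CI falls from 70.1% to 49.8%.

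**The case against.** The strongest reply is that nothing is contradicted. The Design section speaks of outcome measurements in general and does not promise adjudication of the primary composite. The Abstract is open about unblinded assessors, and the Secondary outcomes show where the blinded read is used. A blinded day-7 comparison of ear signs is already planned and tied to a secondary objective, so marked leniency could show there. The detail of a supportive analysis normally belongs in an analysis plan, which is not shown.

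Much of this stands. The read is used, and it is a partial safeguard. What does not stand is that the matter is only omitted detail: the article claims verification and then sets out an endpoint and a sensitivity list that do not carry it out for the primary outcome.

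Three stronger readings are tempting and are not supported:

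- *That the whole problem lies in bulging as the most subjective component.* The documents do not rank the components. Pain is also open to influence, since patients and families know the arm, and no VO read can check it.
- *That the error favours watchful waiting.* The documents give no direction.
- *That false non-inferiority could reach about 30%.* The formula gives 30.3% at f = 20%, but under the 25–50% share assumed above this needs 40–80% of the sign-only failures to be misread, in one arm only.

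**Conclusion.** The concern holds in a limited form. The blinded read is described as verification, yet it cannot alter the primary outcome or any listed sensitivity analysis; the secondary outcomes give only indirect support. A reader might infer that the non-inferiority conclusion will be biased or is invalid. The documents do not show that; they show that the plan has no direct check on the otoscopic part of its primary endpoint.

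The size is illustrative: false non-inferiority of about 5–10% instead of 2.5% if a net 5–10% of watchful-waiting failures are called resolved. This rests on 198 evaluable children per arm, true rates of 80% v 70%, a two-sided 95% CI, error in one arm only, and assumed misclassification rates. Under the one-sided 5% level that reproduces 198, the same errors raise the rate from 5.0% to about 10–17%. The change should be made, but it does not call for a different primary endpoint.

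**What to change.** Keep the GP/nurse practitioner composite as primary. Before unblinding, prespecify one supportive analysis:

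- Re-derive the day-7 composite with bulging and perforation from the blinded VO read. Use the GP/nurse practitioner finding where the VO is missing or unreadable, and take pain, fever and mastoiditis as recorded.
- Report the risk difference and CI against the same 10-point margin.
- Report agreement between the GP/nurse practitioner and the blinded reader, by arm.
- State that the non-inferiority conclusion is qualified if the two analyses disagree.

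If this is not wanted, reword the Design section to say that the blinded read informs secondary outcomes only.

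The cost is small. VO is already scheduled on day 7 (Table 1) and already read blind, and the total of 495 does not change. The reading form must record bulging and perforation separately at day 7; the article names only resolution of signs at that visit, and perforation at week 7. Some recordings will be unreadable and fall back to the unblinded finding, and pain and fever stay unblinded whichever option is chosen.

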### Study setting

The study is a multi-centre study with six participating sites, all of which are in urban settings, including: five Aboriginal Community Controlled Health Services (ACCHSs); and one Indigenous Health Service. ACCHS are services dedicated to health care delivery for Aboriginal Australians and are run by the local Aboriginal communities for the local Aboriginal community and are also known as Aboriginal Medical Services. The Indigenous Health Service has different governance to the ACCHSs, being a state government-supported general practice, which provides primary health care to Aboriginal and Torres Strait Islander peoples. For the purposes of this publication the ACCHSs and the Indigenous Health Service are collectively referred to as health services. The health services are in three states in eastern Australia; two in Queensland (Brisbane), three in New South Wales (Newcastle and Sydney) and one in the Australian Capital Territory (Canberra).

Participants will be recruited from the clients attending the health services. We will obtain informed consent from each participant or their guardian.

### Aboriginal and Torres Strait Islander community ethical consultation and ethical approval

We are committed to conducting this research within the ethical framework recommended by the National Health and Medical Research Council’s Values and Ethics – Guidelines for Ethical Conduct in Aboriginal and Torres Strait Islander Health Research [33] and the Aboriginal Health and Medical Research Council’s key principles for ethical research [34]. We obtained approval from the Boards of the ACCHSs and the Inala Community Jury for Aboriginal and Torres Strait Islander Health Research (a group of Aboriginal and Torres Strait Islander people from the Inala community who guide all research conducted by the service) [35].

This study has been approved by the following ethics committees:Aboriginal Health and Medical Research Council Ethics Committee (938/13)Western Sydney University Human Research Ethics Committee (13/012032 | H10369)Human Research Ethics Committee for the Northern Territory, Department of Health and Menzies School of Health (HOMER 13/2074)Metro South Human Research Ethics Committee (Queensland Department of Health) (HREC/13/QPAH/366)The University of Queensland Medical Research Ethics Committee (2013001093)

### Working with health services and communities

A strong tenet of this research is to work in a culturally safe and productive way with communities and health services, respecting their collaboration and providing them with adequate resourcing. We seek to build capacity both in terms of research skills and knowledge and skills in diagnosis and management of ear disease in these communities and health services. Services have nominated their own associate investigators (AIs) and we have provided funding for research officers (ROs) to be employed in each service. Aboriginal and Torres Strait Islander ROs help to ensure the research is locally culturally appropriate. Community research reference groups nominated by each health service have been funded and supported to provide ongoing community input to the research.

We are training all ROs and health service staff and providing support for professional development of the RO at each site. AIs and ROs are supported to attend annual investigator meetings. Training aims include promoting accurate diagnosis of AOM; the use of tympanometry and VO; evidence-based management of AOM; research skills and culturally appropriate research. The results of all aspects of the trial will be disseminated in each of the communities with which we are working.

